**Study Synopsis**

| **Study title** | A phase 2 pilot study of umbilical cord blood infusion as an adjuvant consolidation therapy in elderly patients with acute myeloid leukemia |
| --- | --- |
| **Indication** | AML consolidation therapy |
| **Objectives** | To assess the efficacy and safety of UCB infusion as an adjuvant consolidation therapy in elderly patients with AML |
| **Study design** | A single-arm, single-center, phase 2 trial |
| **Study center** | Ruijin Hospital affiliated to Shanghai Jiao Tong University  School of Medicine |
| **Participants** | Elderly patients (age ≥ 60 years) with newly diagnosed AML |
| **Study endpoints** | **Primary endpoint**: overall survival (OS)  **Secondary endpoints**: event-free survival (EFS), bone marrow measurable residual disease (MRD), treatment-related adverse events (AEs), and median times to platelet and neutrophil recovery  **Exploratory endpoint**: single-cell RNA sequencing (scRNA-seq) of matched samples collected before and after UCB infusion |
| **Sample size** | 65 elderly patients diagnosed newly with de novo AML were assessed for eligibility and 51 were enrolled. |
| **Inclusion criteria** | 1. Age ≥ 60 years old; 2. Newly diagnosed with de novo AML, examined by bone marrow according to the World Health Organization (WHO) 2022 criteria; 3. Eastern Cooperative Oncology Group (ECOG) performance score 0 to 2; 4. Echocardiography examination of Left Ventricular Ejection Fraction (LVEF) ≥ 50%; 5. Estimated glomerular filtration rate (eGFR) ≥ 60 mL/min, measured using the CKD-EPI formula; 6. Alanine aminotransferase (ALT) ≤ 2.5×upper limit of normal (ULN), aspartate aminotransferase (AST) ≤ 2.5×ULN and total bilirubin ≤ 1.5×ULN; 7. Documented CR after one or two cycles of induction therapies defined according to standard criteria; 8. Inability or unwillingness to undergo allo-HSCT; 9. Signed informed consent before admission to the study. |
| **Exclusion criteria** | 1. Acute promyelocytic leukemia (APL); 2. Secondary AML (sAML); 3. Subjects who had been pretreated with other investigational drugs and/or currently participate in any other clinical trials; 4. Subjects with known involvement of central nervous system (CNS); 5. Subjects with known history of human immunodeficiency virus (HIV) infection; 6. Subjects with known history of hepatitis B virus (HBV) or hepatitis C virus (HCV) infection; 7. New York Heart Association (NYHA) functional classification higher than grade 2; 8. Subjects with chronic respiratory disease requiring continuous oxygen inhalation; 9. Subjects with other malignant tumors or hematological system diseases; 10. Subjects with uncontrolled systemic infection (viral, bacterial or fungal); 11. Subjects with known or suspected autoimmune diseases; 12. Subjects with known history of intolerance or allergy to congeneric drugs; 13. Inability or unwillingness to follow the required protocol procedures; 14. Familial, psychological, geographical or sociological factors potentially impeding compliance with the protocol procedures and follow-up schedules; 15. Any uncontrolled or serious medical disorders that, at the discretion of the investigators, may increase the risks related to study participants or drug administrations, impair the abilities of the patients to undergo protocol therapies or obstruct the data interpretation of the study. |
| **Study treatment** | Two cycles of 15 mg/m2 low dose intravenous decitabine, 1.0 g/m2 intermediate-dose cytarabine, combined with one unite UCB infusion |
| **Efficacy analysis** | **Primary efficacy analysis:**  The primary endpoint of this trial was OS, defined as the time interval from the date of diagnosis to the date of death from any cause, with censoring of patients known to be alive upon the last follow-up.  **Secondary efficacy analysis:**  Secondary endpoints included EFS, bone marrow MRD by flow cytometry, and the median times to platelet and neutrophil count recovery. EFS was determined as the time interval from the date of diagnosis to the date of occurrence of any following events, including relapse or death, whichever came first.  **Exploratory efficacy analysis:**  Blood-based biological characteristics exploratory study analyzed by scRNA-seq of matched pre- and post-UCB infusion samples. |
| **Safety measures** | Treatment-related AEs, including hematological and non-hematological AEs, were defined as those that occurred from the start of treatment. Early deaths were defined as deaths occurring within 30 days of treatment with this regimen. The severity of AEs was assessed following the Common Terminology Criteria for Adverse Events (CTCAE, v5.0) of National Cancer Institute during treatment. |
| **Statistical analysis** | Clinical characteristics of patients were summarized by utilizing frequencies (%) for categorical variables and medians (range) for continuous variables. Fisher’s exact test was used to compare the associations for categorical variables versus categorical variables. Wilcoxon rank sum test was employed to compare categorical variables versus continuous variables. False discovery rate (FDR) corrected by Benjamini-Hochberg approach was applied to adjust the p value for multiple testing unless otherwise specified. Kaplan–Meier survival curves were utilized to evaluate the probabilities of OS and EFS. Log-rank test was performed to compare the survival curves. Asterisks define significance levels. All statistical tests were two-sided unless otherwise specified. Statistical analyses were carried out using R (v4.1.0) packages. |
| **Enrollment time** | 12 January 2015 to 12 February 2022 |
| **Final follow-up** | 31 March 2023 |

**1. Background**

Acute myeloid leukemia (AML) is a clonal malignancy, characterized by aberrant differentiation of hematopoietic stem and progenitor cells. The global incidence of AML increased to 144,645 in 2021, with the age-standardized incidence rate of 1.73/100,000.^1^ Particularly, the incidence of AML increases with age. American and China had the highest incidence cases, with 21,533 and 17,835 AML cases in 2021, respectively.^1^ Moreover, American also showed the highest deaths while China had the highest disability-adjusted life years of AML.^1^

AML treatments consist of initial induction therapy and post-remission therapy. Despite a high initial complete remission (CR) rate after induction therapy,^2,3^ most patients die of relapsed AML. Relapse is the most frequent cause of treatment failure in AML.^4^ Moreover, older patients (age ≥ 60 years) with AML in CR have a much higher relapse rate of 80-90% compared to less than 50% in younger patients.^5,6^ Thus, appropriate post-remission therapy is critical once CR is achieved after induction therapy.

Common post-remission treatment strategies include additional cytotoxic chemotherapy (such as high or intermediate dose of cytarabine) or allogenic hematopoietic stem cell transplantation (allo-HSCT), with or without targeted therapy. Currently, allo-HSCT remains the potentially curative option in patients with AML. Most patients aged ≥ 60 years cannot proceed to allo-HSCT, due to multiple reasons including lack of donor, personal choice and biological factors. As previously reported, only 24% of older patients proceeded to allo-HSCT after intensive therapy.^7^ Meanwhile, targeted therapy may not be available due to lack of targets or lack of access for many patients. Consolidation with chemotherapy is thus administered for these patients. Unfortunately, high or intermediate dose of cytarabine consolidation did not produce prognosis benefits in elderly patients with AML.^8-10^ This leads to highly unsatisfactory outcomes in elderly AML patients. There remains an unmet medical need for these patients.

In recent years, umbilical cord blood (UCB) has emerged as a promising source with effective anti-aging roles,^11,12^ and has been studied for novel indications in malignancies.^13^ UCB has distinct practical advantages of rapid availability, easy collection, more tolerant of Human Leukocyte Antigen (HLA) mismatches, and lower risks of graft-versus-host disease (GVHD).^14^ Given its accessibility, UCB can be available for most of the patients with AML in need. Based on these, we designed a prospective, single-arm, phase 2 clinical trial to investigate the efficacy and safety of consolidation regimen of decitabine and cytarabine combined with UCB infusion in elderly AML patients.

**2. Study Objectives and Endpoints**

2.1 Study Objectives

This study was aimed to evaluate the efficacy and safety of decitabine, cytarabine combined with unrelated UCB infusion as a consolidation therapy in elderly patients with AML after achieving the first CR (CR1).

2.2 Study Endpoints

2.2.1 Primary Endpoint

- Overall Survival (OS): defined as the time interval from the date of diagnosis to date of death from any cause, with censoring of patients known to be alive upon the last follow-up.

2.2.2 Secondary Endpoints

- Event-free Survival (EFS): defined as the time interval from the date of diagnosis to the date of occurrence of any following events, including relapse or death, whichever came first.

- Bone marrow measurable residual disease (MRD) by flow cytometry.

- The median times to recovery of neutrophils (≥ 0.5 × 10⁹/L) and platelets (≥ 20 × 10⁹/L and ≥ 50 × 10⁹/L) documented for each patient.

- Safety: including hematological and non-hematological adverse events (AEs) and the severity of AEs assessed following the National Cancer Institute Common Terminology Criteria for Adverse Events (NCI-CTCAE, v5.0).

2.2.3 Exploratory Endpoint

- Single-cell RNA sequencing (scRNA-seq) of matched samples collected before and after UCB infusion.

**3. Study Design and Planned Sample Size**

3.1 Study Design

This was a prospective, single-arm, open label, phase 2 study evaluating UCB infusion as an adjuvant consolidation regimen in elderly AML patients (ChiCTR-OPC-15006492). This trial was approved by the Human Ethics Committee of Ruijin Hospital affiliated to Shanghai Jiao Tong University School of Medicine (RJ-201646). The protocol was in accordance with Declaration of Helsinki Principles and International Conference on Harmonization (ICH) Good Clinical Practice (GCP) Guidelines. After the institutional review board approval, this trial recruited patients at Ruijin Hospital.

3.2 Planned Sample Size

This study is a phase 2 clinical trial using a single-arm, single-stage design method to calculate the sample size. The primary endpoint is the 2-year OS of all enrolled patients. Based on prior knowledge, the 2-year OS with standard chemotherapy is about 50%. Assuming the 2-year OS expectation with UCB treatment is 67%, with P1 = 0.67 (superior) and P0 = 0.50 (inferior), α = 0.05, β = 0.20, and considering a 5% expected dropout rate, the study plans to enroll approximately 52 patients.

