9.3 Main Results and Analysis Methods

Clinicopathological characteristics of patients were summarized by utilizing frequencies (%) for categorical variables and medians (range) for continuous variables. Fisher’s exact test was used to compare the associations for categorical variables versus categorical variables. Wilcoxon rank sum test was employed to compare categorical variables versus continuous variables. False discovery rate (FDR) corrected by Benjamini-Hochberg approach was applied to adjust the p value for multiple testing unless otherwise specified. Kaplan–Meier survival curves were utilized to evaluate the probabilities of OS and EFS. Log-rank test was performed to compare the survival curves. Asterisks define significance levels. All statistical tests were two-sided unless otherwise specified. Statistical analyses were carried out using R (v4.1.0) packages.

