**15. Progress of the Trial**

- Enrollment start date: 12 January 2015

- Enrollment end date: 12 February 2022

- No. of enrolled patients: 51 cases

- Last follow-up date: 31 March 2023

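### The sample size of about 52 fits α = 0.05 and 80% power only for a one-sided test, but the protocol's general rule makes the primary test two-sided, which gives about 66–72% power

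*Protocol*

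**What the plan says.** Section 3.2 (Planned Sample Size) describes the trial as "using a single-arm, single-stage design method to calculate the sample size". For sizing, "The primary endpoint is the 2-year OS of all enrolled patients". The null rate P0 is 0.50, labelled inferior, and the alternative P1 is 0.67, labelled superior. The rest of the specification is "α = 0.05, β = 0.20, and considering a 5% expected dropout rate, the study plans to enroll approximately 52 patients". Neither the sidedness of α nor the formula is given.

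Section 9.3 (Main Results and Analysis Methods) states "All statistical tests were two-sided unless otherwise specified", and the statistical analysis row of the synopsis repeats the rule. Section 9.3 estimates OS by Kaplan–Meier. It names no test of 2-year OS against 50% and declares no one-sided test. Section 15 (Progress of the Trial) records "No. of enrolled patients: 51 cases", with enrolment and follow-up complete.

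**The concern.** A two-sided default with no exception covers the primary comparison, so the α of 0.05 in section 3.2 should be read as two-sided. On that reading 52 patients is well short of what 80% power requires, and the stated β = 0.20 does not describe the design.

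Sidedness can also decide the result. As a hypothetical illustration, suppose 2-year status were known for all 51 enrolled patients and 32 were alive. The exact binomial p-value against 50% would be 0.046 one-sided and 0.092 two-sided, so the same data would pass one test and fail the other. In an open-label, single-arm trial whose efficacy claim rests on this comparison, the threshold should be legible from the plan and not open to choice once the data are known.

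**Working it through.** **Inputs.** From section 3.2: P0 = 0.50, P1 = 0.67, "α = 0.05, β = 0.20", and the allowance "considering a 5% expected dropout rate". From section 9.3: the two-sided default. Planned enrolment is 52, and 52 × 0.95 = 49.4, so 49 evaluable. Normal quantiles: z = 1.645 (one-sided 0.05), 1.960 (two-sided 0.05), 0.842 (80% power). Per-patient standard deviations of a proportion: √(0.50 × 0.50) = 0.5 and √(0.67 × 0.33) = 0.4702.

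**Step 1: reproduce the plan's 52.**
- Standard one-sample proportion formula, n = [(z_α·0.5 + z_β·0.4702)/0.17]². One-sided this is 51.35, so 52 evaluable; 52/0.95 = 54.7, so 55 enrolled.
- Log-log survival formula. Let θ = ln(−ln S). The difference is ln(0.6931/0.4005) = 0.5486. The per-patient standard deviation, √[(1−S)/(S·(ln S)²)], is 1.4427 at 0.50 and 1.7524 at 0.67. One-sided, n = [(1.645 × 1.4427 + 0.842 × 1.7524)/0.5486]² = 49.2, and 49.2/0.95 = 51.8.

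So 52 including dropout is reproducible, with one-sided α.

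**Step 2: the same inputs, two-sided.**
- Standard formula: [(1.960 × 0.5 + 0.842 × 0.4702)/0.17]² = 65.5, so 66 evaluable; 66/0.95 = 69.5, so 70 enrolled.
- Log-log formula: 61.5 evaluable, and 61.5/0.95 = 64.7.

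**Step 3: power at 49 evaluable (√49 = 7).**
- Standard formula, two-sided: (0.17 × 7 − 1.960 × 0.5)/0.4702 = 0.447, giving 67.2%. One-sided: (1.19 − 0.822)/0.4702 = 0.782, giving 78.3%.
- Log-log, two-sided: (0.5486 × 7 − 1.960 × 1.4427)/1.7524 = 0.578, giving 71.8%. One-sided: 0.837, giving 79.9%.
- Wald (alternative variance throughout), two-sided: 1.19/0.4702 − 1.960 = 0.571, giving 71.6%. One-sided: 0.886, giving 81.2%.
- Exact binomial, two-sided: at least 32 of 49 (upper tail 0.022), power 66.2%. One-sided: at least 31 of 49 (upper tail 0.043), power 76.3%.

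**Summary.** In the enrolled columns, the first number is n/0.95 and the second rounds n up first. The exact rows start from a whole number.

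| Method | One-sided: n, enrolled | Power at 49 | Two-sided: n, enrolled | Power at 49 |
|---|---|---|---|---|
| Standard proportion | 51.3, 54.0–54.7 | 78.3% | 65.5, 68.9–69.5 | 67.2% |
| Wald | 47.3, 49.8–50.5 | 81.2% | 60.0, 63.2–64.2 | 71.6% |
| Log-log | 49.2, 51.8–52.6 | 79.9% | 61.5, 64.7–65.3 | 71.8% |
| Exact binomial (smallest n) | 53, 55.8 | 76.3% | 67, 70.5 | 66.2% |

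**Step 4: does dropout explain the gap?** If all 52 were evaluable, two-sided power would be 70.0% by the standard formula and 65.9% exact. If all 51 enrolled were evaluable, exact power would be 69.5% two-sided and 78.8% one-sided. Removing dropout does not bring two-sided power to 80%.

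**The case against.** The best defence is that single-stage P0/P1 designs are conventionally one-sided and that section 3.2 uses directional labels. The two-sided sentence in 9.3 follows a list of group comparisons (Fisher, Wilcoxon, log-rank), not a one-sample test. Section 9.1 calls the analysis mainly descriptive, and an analysis plan that is not shown may settle sidedness. Much of this stands as evidence of intent: one-sided 0.05 is probably what was used. It does not remove the conflict, because the written rule covers all tests, allows exceptions only where specified, and none is specified in this document.

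Other two-sided formulas might also be tried. The nearest is event-based: [(1.960 + 0.842)/0.5486]² = 26.1 events, divided by the 50% null death rate, gives 52.2. That is before dropout (54.9 after) and counts events at the null rate; at the 33% alternative rate it is 79.0. A log-log formula using the null variance alone gives 54.3, or 57.1 with dropout. Neither yields 52 with dropout included.

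Three stronger readings are tempting but unsupported:
- A reader might infer an arithmetic slip. Step 1 shows that 52 follows from a one-sided calculation.
- A reader might infer that 52 is really the number before dropout, because the standard formula gives 52 at that stage. Section 3.2 says dropout was considered, and the log-log route reaches 52 with it included.
- A reader might turn the exact binomial limits into success cut-offs. The plan censors and uses Kaplan–Meier. Enrolment ended on 12 February 2022 and follow-up on 31 March 2023, less than 14 months later. OS runs from diagnosis, so exact exposure is unknown, but some late enrollees may be censored before 2 years.

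**Conclusion.** The point holds as an internal contradiction between section 3.2 and the two-sided rule in section 9.3 and the synopsis. The stated α, power, dropout and sample size agree for a one-sided test and not for a two-sided one. Under the rule as written, 52 enrolled gives about 66–72% power, so β is about 0.28–0.34 instead of 0.20. Reaching 80% would take about 63–71 enrolled, depending on method, with 70 by the standard proportion formula. Under one-sided 0.05, power is about 76–81%, so the claim of 80% is met or narrowly missed.

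These figures assume 49 patients with known 2-year status and true rates of exactly 50% and 67%. The documents name no method, so no single power figure is the right one. The results do not show that the trial should have enrolled 70, only that the text does not support 80% power on its own terms.

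**What to change.** In section 3.2, state the sidedness of α and the sizing formula actually used. Then take one of two routes:
- If a one-sided 0.05 test was fixed before the data were seen, say so and point to the evidence. Exempt the primary test from the two-sided rule in 9.3 and the synopsis, and give the power for the chosen method at 49 evaluable (76–81% across the methods above).
- If there is no such evidence, keep the two-sided rule, restate the power as about 66–72% (67% by the standard proportion formula), and label any one-sided result post hoc.

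On either route, name the primary test in 9.3 as the Kaplan–Meier estimate of 2-year OS against 50% at the chosen α.

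The cost is wording only. Enrolment is complete, so no patients are added. The downside is that the stated power becomes less favourable, clearly so on the two-sided route.

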**4. Participants**

4.1 Inclusion Criteria:

1. Age ≥ 60 years old;
2. Newly diagnosed with de novo AML, examined by bone marrow according to the World Health Organization (WHO) 2022 criteria;
3. Eastern Cooperative Oncology Group (ECOG) performance score 0 to 2;
4. Echocardiography examination of Left Ventricular Ejection Fraction (LVEF) ≥ 50%;
5. Estimated glomerular filtration rate (eGFR) ≥ 60 mL/min, measured using the CKD-EPI formula;
6. Alanine aminotransferase (ALT) ≤ 2.5×upper limit of normal (ULN), aspartate aminotransferase (AST) ≤ 2.5×ULN and total bilirubin ≤ 1.5×ULN;
7. Documented CR after one or two cycles of induction therapies defined according to standard criteria;
8. Inability or unwillingness to undergo allo-HSCT;
9. Signed informed consent before admission to the study.

4.2 Exclusion Criteria:

1. Acute promyelocytic leukemia (APL);
2. Secondary AML (sAML);
3. Subjects who had been pretreated with other investigational drugs and/or currently participate in any other clinical trials;
4. Subjects with known involvement of central nervous system (CNS);
5. Subjects with known history of human immunodeficiency virus (HIV) infection;
6. Subjects with known history of hepatitis B virus (HBV) or hepatitis C virus (HCV) infection;
7. New York Heart Association (NYHA) functional classification higher than grade 2;
8. Subjects with chronic respiratory disease requiring continuous oxygen inhalation;
9. Subjects with other malignant tumors or hematological system diseases;
10. Subjects with uncontrolled systemic infection (viral, bacterial or fungal);
11. Subjects with known or suspected autoimmune diseases;
12. Subjects with known history of intolerance or allergy to congeneric drugs;
13. Inability or unwillingness to follow the required protocol procedures;
14. Familial, psychological, geographical or sociological factors potentially impeding compliance with the protocol procedures and follow-up schedules;
15. Any uncontrolled or serious medical disorders that, at the discretion of the investigators, may increase the risks related to study participants or drug administrations, impair the abilities of the patients to undergo protocol therapies or obstruct the data interpretation of the study.

**5. Study Procedures**

5.1 Baseline Examination and Screening

1. Medical History Inquiry: Before the start of the study treatment, demographic characteristics including age, sex, smoking history, cancer history, other medical histories (active or cured), comorbidities, and concomitant medications were collected according to the protocol and recorded in the case report form (CRF).
2. Pre-Treatment Baseline Examination:

- To be conducted within 7 days before the start of the study medication.

- Vital signs, physical examination, ECOG score.

- Complete blood count, biochemical routine, coagulation function, EBV-DNA, serum amylase, urine protein and urinalysis, stool routine + occult blood, serum β2-microglobulin (β2-MG).

- Six items of cardiac function, thyroid function, blood type identification, infection screening (hepatitis B, hepatitis C, AIDS, syphilis; if abnormal, complete viral load such as HBV-DNA, HCV-RNA detection).

- Echocardiography, abdominal ultrasound scan, chest CT scan, and electrocardiogram.

- Bone marrow examination: bone marrow smear + flow cytometry MRD detection.

1. Patients who meet the inclusion criteria and do not meet the exclusion criterial were enrolled in the study.

5.2 Study Treatment

Consolidation Therapy:

- Two cycles of 15 mg/m^2^ low dose intravenous decitabine (DAC) over 4h per day for consecutive 5 days (day 1-5), 1.0 g/m^2^ intermediate-dose cytarabine (Ara-C) at q12h for consecutive 2 days (day 6-7), combined with one unit UCB infusion on day 9.

- No immunosuppression was given as prophylaxis for GVHD, unless acute GVHD (aGVHD) was documented or clinically diagnosed.

Selection of UCB:

- High-resolution Human Leukocyte Antigen (HLA) typing for HLA-A, B, and DR loci was performed in all enrolled patients.

- The UCB units were obtained from the cord blood bank at the China Shandong Cord Blood Bank Network if they met the following criteria:

a). Serologically matched of four or five of six HLAs.

b). Contained at least 3 × 10⁷ nucleated cells/kg of recipient body weight before freezing.

Maintenance Therapy:

- Decitabine 15 mg/m² for 5 days, every 28-day cycle.

OR

- Azacitidine 75 mg/m² for 7 days, every 28-day cycle.

